### Participants

#### Diagnostic criteria

The diagnostic criteria for this trial will be set based on the American Diabetes Association guidelines [7], Chinese Diabetes Society guidelines [8], National Kidney Foundation Kidney Disease Outcomes Quality Initiative (NKF-KDOQI) guidelines [30] and Kidney Disease Improving Global Outcomes (KDIGO) 2012 Clinical Practice Guideline [31]. For a diagnosis of early-stage DKD, patients with DM will have to present the following conditions:
Diagnosed with type 2 diabetesPatients with type 2 diabetes with microalbuminuria and urinary microalbumin excretion rate (UAER)
For microalbuminuria, two repeated tests performed within 6 months will need to produce abnormal resultsUAER of 30–300 mg/24 h or urinary albumin-to-creatinine ratio (ACR) of 30–300 mg/g (mg/mmol)Have clinical manifestations of kidney diseases, such as edema, anemia, renal dysfunction, etc.

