### Intervention

All subjects in the two groups will receive the conventional treatment, including oral losartan (50 mg/once a day), diet, exercise and oral medicine, to ensure access to steady levels of blood glucose, blood lipids and blood pressure, based on the recommendations of the American Diabetes Association guidelines [7] and Treatment of Chinese Diabetes Society guidelines [8]. Subjects will be randomly assigned to receive placebo (6 g/bag twice per day) or Tangshan Formula (6 g/bag twice per day) by specified sequence number from the central randomization system. The treatment will last for 24 consecutive weeks.

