### Outcomes

#### Primary outcomes

Urinary microalbumin (MAlb) is a critical indicator for the diagnosis of early renal impairment in diabetes mellitus. For early-stage DKD, the urinary microalbumin–creatinine ratio (ACR) will be a primary evaluation index. The change in ACR from baseline will be evaluated between the two groups, and the ACR will be compared at baseline and treatment endpoint (24 weeks) in each group.

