### Statistical analysis

The statistical analysis of this study was completed by an independent statistician, and the detailed statistical analysis plan was formulated separately by a statistician before the inception of this trial and determined with the Principal Investigator. Three analysis sets will be used for assessment of this study: the intention-to-treat set (ITT), the per-protocol analysis set (PPS) and the safety analysis set (SAS). The ITT and PPS will be used to appraise the efficacy of TSF. If any given case exists missing a critical variable, the last observation used as the final results will be carried forward to the final data. The changes of urinary microalbumin–creatinine ratio, urinary microalbumin, GFR, creatinine and baseline information will be present after treatment. A paired *t* test or the Wilcoxon signed-rank test will be employed to compare each group. Changes relative to baseline after treatment will be compared between groups using the *t* test or the Wilcoxon rank-sum test. *P* < 0.05 will be deemed to show a statistically significant difference.

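### The unadjusted test on change in ACR is valid but gives up power that log ACR with baseline adjustment would recover, and before-after tests within each arm do not belong under the primary outcome

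*Protocol article*

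**What the plan says.** The Primary outcomes section of the protocol article gives two comparisons. The first is between arms: "The change in ACR from baseline will be evaluated between the two groups". The second is inside each arm: "the ACR will be compared at baseline and treatment endpoint (24 weeks) in each group".

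The Statistical analysis section assigns tests to both. Between arms, "Changes relative to baseline after treatment will be compared between groups using the" t test or the Wilcoxon rank-sum test. Within arms, a paired t test or Wilcoxon signed-rank test "will be employed to compare each group". One threshold, P < 0.05, covers all of them. No covariate and no transformation is named. The section adds that "the detailed statistical analysis plan was formulated separately by a statistician before the inception of this trial"; that plan is not shown.

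Three design features bear on this:
- Intervention: "All subjects in the two groups will receive the conventional treatment, including oral losartan".
- Exclusion criteria: losartan is exempt from the bar on recent ACEI or ARB use but is not required, so some patients may start it on study.
- Diagnostic criteria: entry is by albumin excretion rate or by "urinary albumin-to-creatinine ratio (ACR) of 30–300 mg/g", a tenfold window on the outcome variable itself.

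**The concern.** There are two separate concerns.

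**Efficiency of the between-group test.** With a tenfold entry range and the right skew that one would assume for ACR, a mean raw change is dominated by patients with high values. A test on change without a baseline covariate also fixes the baseline coefficient at 1 instead of estimating it. Neither feature makes the test invalid. Both can cost power that data already in the schedule would recover.

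**Within-arm tests under the primary outcome.** A before-after change in the TSF arm mixes any TSF effect with losartan, the rest of conventional care and regression to the mean. Only the contrast between arms removes these. Listing the within-arm comparison beside the randomised one invites a reader to take a significant fall in the TSF arm as evidence for TSF.

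**Working it through.** **The plan's own figures.** The Sample size section sizes the trial on a responder rate (ACR reduced by 50% or more), so it gives no power for a test on change in ACR. Its 275 per arm is used below only as an arm size. The printed formula with 12.5% and 18.7% in fact gives 423 per arm; that is a separate matter, and nothing here depends on it.

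**Assumed inputs.** The protocol gives no ACR SD, no baseline to week-24 correlation and no target difference in ACR. Assumed: 275 per arm; baseline log-uniform on 30–300 mg/g; log week-24 ACR linear in log baseline with slope b = 0.6–1.0; residual log-SD 0.8; true TSF/placebo ratio 0.80; two-sided 0.05.

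**Log scale, closed form.**
- Baseline log variance: (ln 10)²/12 = 0.442.
- ANCOVA residual variance: 0.8² = 0.64.
- Log-change variance: (1 − b)² × 0.442 + 0.64 = 0.711, 0.658 and 0.640 for b = 0.6, 0.8 and 1.0.
- Variance ratio, ANCOVA to log change: 0.64 divided by these = 0.90, 0.97 and 1.00. Baseline adjustment therefore saves 10%, 3% and 0%.
- ANCOVA power: SE = 0.8 × √(2/275) = 0.0682; |ln 0.80| = 0.2231; 0.2231/0.0682 = 3.27; Φ(3.27 − 1.96) = 0.905.
- Log-change t test at b = 0.6: SE = √(2 × 0.711/275) = 0.0719; 0.2231/0.0719 = 3.10; Φ(3.10 − 1.96) = 0.87.

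**Simulated power, same inputs, b = 0.6–1.0.**

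| Between-group analysis | Power |
|---|---|
| t test, raw change | about 65–72% |
| Wilcoxon rank-sum, raw change | about 78–84% |
| t test, log change | about 87–91% |
| ANCOVA, log ACR | about 91% |

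Most of the step is from raw to log scale; adjustment adds a few points at most.

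**A second model.** Here log-normal ACR is truncated to 30–300 at baseline, the TSF ratio is 0.85, and the between-/within-person log-SDs are 0.6/0.4, 0.6/0.6 and 0.5/0.7. Power in these three settings:

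| Analysis | 0.6/0.4 | 0.6/0.6 | 0.5/0.7 |
|---|---|---|---|
| t, raw change | 76% | 48% | 42% |
| Wilcoxon, raw change | 80% | 51% | 42% |
| t, log change | 94% | 64% | 57% |
| ANCOVA, log ACR | 95% | 70% | 66% |

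Adjustment adds about 1, 6 and 9 points, more as baseline predicts week 24 less well. In the textbook case of equal variances at both times, the ratio is (1 + ρ)/2: 0.65, 0.75, 0.85 and 0.95 for ρ = 0.3, 0.5, 0.7 and 0.9. Then 275 per arm on change scores matches 179, 207, 234 and 262 with ANCOVA.

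**No TSF effect, between arms.** Type I error was about 3–7% for every between-group method, including runs with a shared losartan effect (simulation error 1–2 points).

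**No TSF effect, within the TSF arm** (first model, b = 0.8, log-SD 0.8). With a shared 10–15% fall, signed-rank on log change was significant in 53–90% of trials, but signed-rank on raw change in only 5–31%. At the 10% fall, the raw paired t test showed a significant rise in about 55% of TSF arms, while signed-rank on log change showed a significant fall in about 55%. In the second model, the pattern of TSF arm significant and control arm not occurred in up to about 27% of null runs.

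**The case against.** The strongest reply has four parts.

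1. **Losartan.** A reader might infer that this analysis lets losartan pass as a TSF effect. The documents do not support that for the between-group test: both randomised arms receive losartan, so its effect cancels, and simulated type I error stays near nominal. The inference holds only if a within-arm result is read as efficacy. The protocol nowhere says that it will be, and the abstract gives the primary outcome simply as the change in ACR. This part of the reply stands in full.

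2. **Size of the adjustment gain.** A reader might quote a 15–35% variance saving from (1 + ρ)/2 with ρ = 0.7–0.3. That formula needs equal variances at baseline and week 24, which the first model does not have; there the saving is 0–10%. This also stands.

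3. **Scale and skew.** The protocol does not say that change means raw change, and it offers a rank test. Against Wilcoxon, the first-model gap narrows to 78–84% versus about 91%. This limits the size, but a gap remains, and a rank test by itself yields no estimate of the ACR ratio.

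4. **Unseen plan.** Transformation, covariates and the rule for choosing between t and Wilcoxon may stand in the separate analysis plan. Their mere absence from an article is no finding. But the article does name an unadjusted test on change and does place within-arm comparisons under the primary outcome. Those statements are open to improvement as written, and an analysis plan that differs would have to be reconciled with them.

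**Conclusion.** The point holds as a recommendation on efficiency and on labelling, not as a charge of bias. The named between-group test is valid under randomisation. Under the first set of assumptions it has about 65–84% power on raw change, depending on the test, against about 91% for log-ACR ANCOVA; most of that difference is due to the log scale. The ranking is the same under the second set, where ANCOVA leads by roughly 15 to 24 points. All these levels rest on assumed SDs, slopes and effects that the protocol does not give, so the direction is firmer than any single figure.

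Separately, the within-arm before-after tests are not randomised comparisons. Their outcome can change, and even reverse direction, with scale and test. They should not sit under the primary outcome. The share of patients who start losartan on study is unknown, so its contribution to those changes cannot be sized.

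**What to change.** - Name one primary analysis: ANCOVA on log week-24 ACR with treatment and log baseline ACR, reported as a ratio of geometric means with 95% CI. Centre and losartan use at screening are optional covariates.
- Keep the Wilcoxon rank-sum test on change as a sensitivity analysis.
- Remove the within-arm paired tests from the primary outcome, and report arm-level changes descriptively without P values.
- If the separate analysis plan already says this, bring the article's wording into line with it.

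The cost is wording only. Table 1 already schedules ACR at baseline and week 24 and records treatment history and medication. The Trial status section reports 95 patients recruited with recruitment continuing, and the Blinding section keeps allocation masked until completion, so the change can be made and dated while blinded.

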### Bias analysis

The main evaluation outcome of this trial is the rate of progression from microalbuminuria into clinical proteinuria, which is very objective. Although ACEI and ARB drugs have achieved a recognized efficacy internationally, a certain proportion of patients still cannot delay the progression of DKD even using these two drugs. Therefore, the bias factors affecting the outcome evaluation include three aspects: blood glucose level; ACEI and/or ARB use; and laboratory testing error for urine microalbuminuria.

These factors are solved as follows: for the blood glucose level, the consistency of this factor in the two groups is ensured due to the random and double-blind study design method; subjects only take losartan and no other ARB or/and ACEI drugs; and central laboratories are used for the main outcomes.

## Discussion

DKD is part of the systemic microangiopathy and glomerular sclerosis caused by diabetes. In European and American countries, DKD is the primary cause of renal replacement therapy, accounting for about 1/2. It is the second common cause of ESRD in China after glomerular disease [1]. Compared to CKD from non-diabetic causes, DKD develops more rapidly into ESRD [34, 35]. It is urgent to seek an effective preventive measure to delay DKD. CHMs have been common in treating DM [36–41] and its complications [24, 42, 43], including DKD. In modern times, many patients have turned to Chinese herbal medicine for treatment as a complementary and necessary combination-drug therapy for kidney disease in China due to its fewer adverse reactions and more effective interventions. Currently, research from Taiwan has demonstrated that patients with CKD who used CHM had a significantly reduced ESRD risk (60%) [44]. Relevant clinical observations have shown that TSF appears to prevent further development and deterioration of the disease, which includes the reduction of urinary albumin and normalization of the glomerular filtration rate [45–47]. Potential mechanisms have proved that herbal medicine could regulate oxidative stress, which is well recognized to play a significant role in the worsening of DKD [45, 48, 49]. However, there was less clinical research on delaying the progression of DKD, especially in the early stage as the only period of reversing kidney lesions [50]. This work has the potential function to delay the development of DKD. Therefore, we are implementing this study to evaluate the efficacy and safety of TSF treatment for DKD. If successful, this work will provide evidence-based medical evidence for a therapeutic approach to delaying the progress of DKD.

### Trial status

Patient recruitment began in May 2018 and was expected to be completed in May 2022. At the time of manuscript submission, 95 patients had been recruited and the estimated time of recruitment completion is May 2020. Currently, we are still recruiting participants. Protocol version number 20,160,718 protocol02 (date 18 October 2016).

## Abbreviations

ACEI: Angiotensin-converting enzyme inhibitor
ACR: Albumin-to-creatinine ratio
AE: Adverse event
ARB: Angiotensin II receptor blocker
CHM: Chinese herbal medicine
CKD: Chronic kidney disease
CRF: Case report form
CRO: Clinical research organization
DKD: Diabetic kidney disease
ESKD: End-stage kidney disease
GFR: Glomerular filtration rate
ITT: Intention-to-treat set
KDIGO: Kidney Disease Improving Global Outcomes
MAlb: Urinary microalbumin
NKF-KDOQI: National Kidney Foundation Kidney Disease Outcomes Quality Initiative
PPS: Per-protocol analysis set
RAAS: Renin–angiotensin–aldosterone system
SAS: Safety analysis set
SCr: Serum creatinine
SOP: Standardized operation practice
TSF: Tangshan Formula
UAER: Urinary microalbumin excretion rate
